## Blinding

Blinding of group allocation will not be possible for the LAC who will complete the self-report follow up assessment or for those delivering the intervention. The study statistician and health economist will be blind to group allocation and will only have details of participant by study number. However, as this is a pilot feasibility trial, the SOLID researchers will be carrying out both process and follow up evaluation so may become aware of study allocation as the trial progresses.

## Unblinding

The trial statistician and health economist will only be unblinded after the final analysis or if requested to do so due to safety concerns expressed by the Trial Oversight Committee.

### Schedule of Events

Table 1 RCT showing Schedule of Events

| **Procedures** | **Visits (insert visit numbers as appropriate)** | | | | | | | | |
| --- | --- | --- | --- | --- | --- | --- | --- | --- | --- |
|  | **Screening** | **Baseline (pre randomisation)** | **Intervention Phase 6 sessions over maximum of 12 weeks** | | | | | | **12 month follow up from baseline** |
|  |  |  | Session 1 | Session 2 | Session 3 | Session 4 | Session 5 | Session 6 |  |
| Informed consent |  | X |  |  |  |  |  |  |  |
| Demographics |  | X |  |  |  |  |  |  |  |
| Placement type |  | X |  |  |  |  |  |  |  |
| Eligibility assessment | X | X |  |  |  |  |  |  |  |
| CRAFFT | X |  |  |  |  |  |  |  |  |
| Randomisation |  | X |  |  |  |  |  |  |  |
| Intervention (MET or SBNT) |  |  | X | X | X | X | X | X |  |
| Self-reported Drunkenness |  |  |  |  |  |  |  |  | x |
| AUDIT |  | X |  |  |  |  |  |  | X |
| ASSIST |  | X |  |  |  |  |  |  | X |
| SDQ |  | X |  |  |  |  |  |  | X |
| WEMWBS |  | X |  |  |  |  |  |  | X |
| EQ-5D-5L |  | X |  |  |  |  |  |  | X |
| TLFB-30 |  |  |  |  |  |  |  |  | X |
| Placement Stability questions |  |  |  |  |  |  |  |  | X |
| ALSPAC CASI + ESPAD questions on sexual behaviour |  |  |  |  |  |  |  |  | X |
| Antisocial / criminal behaviour questionnaire |  |  |  |  |  |  |  |  | X |
| Use of health and social services |  |  |  |  |  |  |  |  | X |
| Adverse event assessments |  | X | X | X | X | X | X | X | X |

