**TRIAL SUMMARY**

| **Trial Title** | **SOLID (Supporting Looked After Children and Care Leavers In Decreasing Drugs, and alcohol):** a pilot feasibility study of interventions to decrease risky substance use (drugs and alcohol) and improve mental health of Looked After Children and Care Leavers aged 12 -20 years |
| --- | --- |
| **Acronym** | SOLID |
| **Summary of Trial Design** | Pilot feasibility randomised controlled trial |
| **Summary of Participant Population** | Looked After Children and Care Leavers (LAC) aged 12-20 years who screen positive for being at risk of early drug and alcohol use (≥ 2 in the CRAFFT). |
| **Planned Sample Size** | Phase 1 Formative Research  20 1:1 interviews with LAC  20 1:1 interviews with Carers  1 focus group with professionals  1 focus group with Drug and alcohol workers  Pre pilot trials  5 1:1 interviews with LAC trialing the interventions  5 1:1 interviews with Drug and Alcohol workers trialing the interventions  LAC leads survey:  Surveys with all named LAC Community Pediatric leads in each local authority in England (n=152).  Intervention finalization workshop  1 focus group with Professionals  1 focus group with LAC and Carers  Phase 2 Pilot RCT  Sample size required - minimum of 35 LAC per arm at follow-up (3 arm trial). Aim to recruit 150 LAC in total to allow for 30% loss to follow-up.  Process Evaluation  20 1:1 interviews with LAC  20 1:1 interviews with Carers  15 1:1 interviews with Drug and alcohol workers  1 focus group with Social Workers  1 focus group with Drug and alcohol workers |
| **Planned Number of Sites** | 5 (Newcastle, Durham and Teesside (Middleborough, Stockton and Redcar) |
| **Intervention Duration** | 6 sessions over a maximum of 12 weeks |
| **Follow Up Duration** | 12 months (+8 week window) |
| **Planned Study Period** | 24 months |

| **Intervention arms** | 2 active intervention arms:   - 6 sessions of Motivational Enhancement Therapy (MET) or - 6 sessions of Social Behavioural Network Therapy (SBNT)   Interventions will take place over a maximum of a 12 week period. |
| --- | --- |
| **Control arm** | Usual social worker delivered care with additional signposting to local drug and alcohol third sector services. |
| **Inclusion criteria** | - LAC aged 12-20 years - Screen positive for at risk of substance misuse i.e. scoring ≥ 2 on the CRAFFT screening questionnaire - Consents to take part in the study |

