**Economic tool development and value of information analysis**

**Ongoing: Process evaluation** -mixed methods including: trial recruitment and retention, intervention adherence and satisfaction: **STOP/GO criteria assessed**

**SOLID Admin Lead**: completes stratified randomisation & group allocation. Admin lead contacts;

1. LAC, and carer with the outcome of allocation;

2. Drug and alcohol services for those allocated to intervention arms.

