## Recording and Reporting AEs and SAEs

All AEs and SAEs occurring from the time of randomisation in the Pilot RCT until follow up is completed (12 months post enrolment) must be reported. Depending on the nature of the event, the reporting procedures below should be followed. Any questions concerning adverse event reporting should be directed to the Chief Investigator or the Study Coordinator (Research Associate) in the first instance.

**Adverse Event (AEs):** All non-serious adverse events (as defined in section 9.1 above and including non-serious adverse reactions) during study participation must be recorded on an adverse event/harms case report form and sent to the Study Coordinator within 2 weeks of the event. Severity of AEs will be graded on a three-point scale (mild, moderate or severe). The Study Coordinator will enter the data onto the study database. In addition, the Study Coordinator will contact the LAC team manager monthly to ensure no adverse events are missed.

Expected AEs include the following:

- Severe drug and alcohol use
- Mental health difficulties
- Self-harm and suicidal ideation

**Serious Adverse Event (SAEs):** All SAEs (as defined in section 9.1 above and including serious adverse reactions) during study participation must be reported to the Chief Investigator within 24 hours of the site becoming aware of the event. The initial report should ideally be made by completing the study SAE form and sending via the fax number listed on page 64 of the protocol. Alternatively, if this is not possible, the initial report may be made by telephone to the number listed on page 64 of the protocol. In the case of incomplete information at the time of initial reporting, all appropriate information should be provided as follow-up as soon as this becomes available. Relationship of the SAE to study procedures will be assessed by the Chief Investigator, as will the expected or unexpected nature of the SAE.

As the study deals with a vulnerable population, expected SAEs include those related to the following which result in hospitalisation:

- Severe drug and alcohol use
- Mental health difficulties
- Self-harm and suicidal ideation

SAEs exclude:

- any pre-planned hospitalisations (e.g. elective surgery) not associated with clinical deterioration
- routine treatment or monitoring of the studied indication, not associated with any deterioration in condition

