## Responsibilities

***Chief Investigator***

- *Clinical oversight of the safety of trial participants, including an ongoing review of the risk/benefit.*
- *Using medical judgement in assigning seriousness, causality and expectedness of SAEs where it has not been possible to obtain local assessment.*
- *Using medical judgement in assigning expectedness to SARs*
- *Immediate review of all USARs.*
- *Review of specific SAEs and SARs in accordance with the trial risk assessment and protocol.*
- *Checking for AEs and ARs when participants attend for treatment or follow-up*
- *Ensuring that all SAEs and SARs, including USARs, are recorded and reported to the Sponsor within 24 hours of becoming aware of the event and provide further follow-up information as soon as available.*
- *Ensuring that AEs and ARs are recorded and reported to the Sponsor in line with the requirements of the protocol.*
- *Expedited reporting of USARs to the REC within required timelines*
- *Notification to all investigator sites of any USAR that occurs*

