***TOC***

- *Review of safety data collected to date to identify any trends*

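### Adverse event ascertainment is closer in the MET and SBNT arms than in control during the intervention period, so event counts by arm may be inflated for the active arms unless the source of each report is recorded

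*Protocol*

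**What the plan says.** The relevant provisions are all in the protocol.

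- **Section 5.7.1, Table 1.** The row "Adverse event assessments" is marked at baseline, at Sessions 1 to 6 and at the 12-month follow-up. The session columns stand under the heading "Intervention Phase 6 sessions over maximum of 12 weeks". The only other row marked in them is the delivery of MET or SBNT.
- **Trial Summary, control arm.** Controls receive "Usual social worker delivered care with additional signposting to local drug and alcohol third sector services".
- **Figure 2 (phase 2 flow diagram).** After allocation the admin lead contacts "Drug and alcohol services for those allocated to intervention arms".
- **Section 9.4, Chief Investigator.** One listed duty is "Checking for AEs and ARs when participants attend for treatment or follow-up".
- **Section 9.2.** The reporting duty covers "All AEs and SAEs occurring from the time of randomisation in the Pilot RCT until follow up is completed" at 12 months, with no distinction by arm. It adds that "the Study Coordinator will contact the LAC team manager monthly to ensure no adverse events are missed".
- **Section 9.4, TOC.** The committee's task is "Review of safety data collected to date to identify any trends".

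**The concern.** Scheduled adverse event checks follow the delivery of therapy. Two arms have up to six face-to-face occasions within 12 weeks at which an event can come to light. The third has no scheduled direct check between randomisation and month 12.

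The events that section 9.2 lists as expected are severe drug and alcohol use, mental health difficulties, and self-harm and suicidal ideation. It is plausible, though the protocol does not say so, that a young person would mention some of these in a counselling session when a team manager would not hear of them. More recorded events under MET or SBNT could then reflect closer observation, and a real excess could not be told apart from it.

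The stakes are modest but not nil. The TOC looks for trends in these data, and section 5.7 allows its safety concerns to lead to unblinding of the statistician and health economist. The pilot also informs a definitive trial, which could inherit the same schedule.

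**Working it through.** The protocol gives no event rate and no capture rate, so there is no stated figure to reproduce. Two checks are possible.

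**1. Count of scheduled occasions.** The baseline mark in Table 1 is left out, because it is before randomisation and section 9.2 starts reporting at randomisation.

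| Occasions after randomisation | MET or SBNT | Control |
|---|---|---|
| Sessions (Table 1) | 6 | 0 |
| 12-month visit (Table 1) | 1 | 1 |
| **Table 1 total** | **7** | **1** |
| Monthly manager contacts over 12 months (9.2) | 12 | 12 |
| **With manager contacts** | **19** | **13** |

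19/13 = 1.46 if all six sessions are attended. The stop/go criteria refer to attending at least 60% of sessions: 0.60 × 6 = 3.6, so 4 sessions. At that attendance the count is 17 against 13, and 17/13 = 1.31. These are ratios of occasions only. A manager contact is one call to a team and is not a check on a named participant, so it cannot be weighted like a session.

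**2. Illustration of the effect on recorded events.** Every capture rate here is an assumption. Let:

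- *s* be the chance that the sessions pick up an event occurring in a 12-week window (active arms only);
- *m* be the chance that the all-arm routes of section 9.2 pick up an event before month 12;
- *r* be the chance that the 12-month visit picks it up (all arms).

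Assume equal true event rates, events spread evenly over 52 weeks, and independent routes. Then:

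- control: C = 1 − (1 − m)(1 − r)
- active, in the window: A = 1 − (1 − s)(1 − m)(1 − r)
- active, over 12 months: (12/52) × A + (40/52) × C

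Example with s = 0.8, m = 0.3, r = 0.2:

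- C = 1 − 0.7 × 0.8 = 0.44
- A = 1 − 0.2 × 0.7 × 0.8 = 0.888
- ratio in the window: 0.888/0.44 = 2.02
- active over 12 months: 0.231 × 0.888 + 0.769 × 0.44 = 0.543, and 0.543/0.44 = 1.23

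Active-to-control ratios of recorded events, for s from 0.5 to 0.8 and r from 0.2 to 0.8:

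| m | Over 12 months | Within the 12-week window |
|---|---|---|
| 0 | 1.03 to 1.74 | 1.12 to 4.2 |
| 0.3 | 1.02 to 1.23 | 1.08 to 2.02 |
| 0.6 | 1.01 to 1.09 | 1.04 to 1.38 |
| 0.9 | 1.00 to 1.02 | 1.01 to 1.07 |

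The first row ignores section 9.2 and is shown only as a limit. In every row the tilt is towards more recorded events in the active arms. Its size depends almost wholly on how well the all-arm routes work, which the protocol does not quantify.

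**The case against.** The case on the other side is substantial.

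- **All-arm reporting.** A reader might infer from Table 1 that control events reach the trial only through the manager before month 12. Section 9.2 does not support that. Adverse events in any arm go on a form within 2 weeks, SAEs are due within 24 hours of the site becoming aware, and the manager contact is an addition to this duty. Section 9.5 adds all deaths. This stands, and it is why the offset counts as real though partial.
- **Progression.** A reader might infer that a false signal would affect the decision on a definitive trial. No stop/go criterion uses adverse events, and acceptability is judged from interviews and focus groups. This also stands.
- **TOC review.** Section 9.4 does not say that trends are examined by arm. Section 13 sets three meetings, at the start of the study and at the end of each phase. So a comparison by arm is possible but not prescribed.
- **Nature of the comparison.** Unequal contact is inherent when a talking therapy is compared with usual care. That explains the imbalance but does not remove it. Section 6.2 mentions control workers in the drug and alcohol teams, but no adverse event assessment is scheduled with them.
- **Left to the analysis plan.** Tabulation by arm can properly be left to an SAP that is not shown. Recording the route of detection cannot, because it has to be captured when the event is reported. The SAE items listed in section 9.2 do not include it. The nearest item, an identifiable reporter in section 9.3, applies to USARs only. The forms themselves are not shown.
- **Hiding harm.** An arm summary limited to common sources would leave out self-harm or suicidal ideation disclosed in sessions. This stands, so a common-source summary should never appear alone.

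**Conclusion.** The point holds as a minor one. Followed as written, the protocol gives unequal adverse event ascertainment by arm during the intervention period: seven scheduled assessments after randomisation against one. The reporting duty and the monthly manager contact offset this only in part. Counts may be inflated for MET and SBNT, chiefly for non-serious events; SAEs leading to hospitalisation are less exposed.

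The documents do not allow the amount to be estimated. The 12-month ratios of about 1.00 to 1.23, with *m* at 0.3 or more, rest on assumed capture rates, equal true event rates and independent routes.

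Two stronger readings are not supported. A reader might infer that the active arms will certainly show more events through detection alone, but if the all-arm routes work well the difference is negligible. A reader might also take 19 against 13 occasions as a 46% bias, but that is a count of unlike contacts at full session attendance and says nothing about how many events are missed.

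**What to change.** 1. In section 9.2, add a source-of-report field to the adverse event form and the SAE form, with the options session, manager contact, 12-month visit and other.
2. State in section 9.2 and in the TOC item of section 9.4 that any summary by arm shows all events and, beside them, events from sources common to all arms, with a note that session-based detection applies only to the active arms.
3. State that no event is dropped from reporting or safety review, whatever its source.

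The cost is one form field and one extra table. No visit is added. A limit remains: the common-source comparison may keep some detection bias, because a need uncovered in a session can lead to onward referral under section 6.3 and then reach the manager, which can happen only in the active arms.

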## Withdrawal Criteria

Participants have the right to withdraw from the trial at any time without having to give a reason. The team will try to ascertain the reason for withdrawal and document this reason within the Case Report Form.

The Investigator may discontinue a participant from the trial at any time if the Investigator considers it necessary for any reason including:

- Participant withdrawal of consent
- Investigator’s discretion that it is in the best interest of the participant to withdraw
- An adverse event that requires discontinuation of the trial intervention or renders the participant unable to continue in the trial
- Termination of the trial by the sponsor

Participants who withdraw from the trial will not be replaced.

Participants may withdraw from study intervention and/or from follow-up data collection. Participants requesting withdrawal from intervention will be asked if they would be willing to remain in the study for purposes of follow-up data collection as per schedule of events. Data provided to the point of withdrawal will be retained.

## Storage and Analysis of Samples

No biological samples will be collected as part of this study. Identifiable data will be destroyed after 10 years.

## End of Trial

The end of the trial will be considered as the last participant’s follow-up visit at 12 months.

# TRIAL INTERVENTIONS

## Name and Description of Interventions

The adapted interventions based on MET and SBNT will be delivered by existing drug and alcohol team workers.[^32^](#_ENREF_32)^,^ [^33^](#_ENREF_33) These workers will be specifically trained to deliver the study interventions. The key areas of contrast between MET and SBNT are summarised in Table 2.

Table 2 Contrasts between MET and SBNT

(taken from Copello et al 2009 with permission from the author)

| MET | SBNT |
| --- | --- |
| The individual’s motivation is central to addiction process. An increase in the individual’s motivation to change will increase likelihood of success | Positive social support for change is central to addictive process |
| Aim to alter the individuals decisional balance and to amplify discrepancy between current use of alcohol and future goals | Aims to maximise outside positive support for change |
| The therapist discusses motivation as seen by the client | Therapist is an active agent for change within the problem drinkers social environment |
| Significant others play some role in treatment but are not central | The Therapist always attempts to engage significant others that are central to the behaviour change process |
| The therapist elicits reasons for change from the “problem drinker” using a number of techniques | The therapist acts as a team leader, leading the team to the attainment of specific goals. |

Behaviour Determinants Intervention (BDI)[^53^](#_ENREF_53) theory of change models for MET and SBNT are presented in Figures 3 and 4 respectively on pages 39 and 40. Both models explain the proposed change pathways for the interventions, highlighting the determinants for change and key behaviours targeted.

**Motivational Enhancement Therapy (MET)** is a client centred, directive counselling approach developed within the NIH MATCH study as a concentrated version of motivational interviewing which adds a problem feedback component to standard treatment. [^32^](#_ENREF_32)^,^ [^54^](#_ENREF_54) The intervention has been shown to decrease substance use in a range of participants including adolescents.[^34^](#_ENREF_34)^,^ [^54^](#_ENREF_54) The basic assumption of MET is that the motivation and responsibility for change lie within the client and it is the therapist’s role to create an environment to enable the client to change. Unlike cognitive behavioural interventions, ambivalence is assumed to be the norm and motivation is formed and enhanced within the context of the therapist-client relationship. The therapist employs specific strategies to develop motivation, seeking to mobilize the client’s inner resources and intrinsic motivation and in doing so, enables the client to initiate and achieve behaviour change.

The therapist supports the client to explore their substance use and elicits their own concerns and motivations. By reflecting and reaffirming this ‘change talk’,[^55^](#_ENREF_55) a discrepancy is developed between where the client currently is and where they want to be; tipping the decisional balance in favour of change. Motivation is further built through self-motivational statements, strengthening the commitment to change, which is negotiated through a plan for change. Personal responsibility for change is encouraged. This is in contrast to cognitive behavioural approaches which teach clients the skills needed to change. Within the follow-through phase, the therapist’s role is to review progress that the client has made against their self-chosen goals and strategies. Motivation to change is renewed by this process and self-efficacy is reaffirmed.[^32^](#_ENREF_32)

Figure 3 BDI Theory of change model for MET

**
[figure not shown]
**

**Social Behavioural Network therapy (SBNT)** is a systematic counselling approach, which utilises cognitive and behavioural strategies to help clients build social networks supportive of positive behaviour change in relation to problem substance misuse and goal attainment.[^56^](#_ENREF_56) SBNT is based on the premise that social network support for change is key in helping people deal effectively with addictive behaviour. The intervention focuses on addressing substance use by engaging with a network of positive support for lifestyle change. This work is conducted in collaboration with the young person with whom early identification of the social network is carried out. An important aspect of SBNT, especially important for LAC, is that it aims to sustain engagement with vulnerable young people by widening the reach of the intervention beyond the traditional family to include supportive peers or other important figures as perceived by the young person including e.g. teachers, social workers or possibly wider family members such as grandparents.

The theoretical basis of the approach is informed by evidence of the positive influence of social support and support for behaviour change in improving substance use. Alcohol treatment research in adult populations has shown that general social support, alcohol-specific social support and the drinking behaviour of the social network members have all been shown to be unique predictors of positive alcohol treatment outcomes.[^56-59^](#_ENREF_56)

Informed by previous research, the intervention aims to integrate strategies found to be effective in other family and network approaches and, is based on the concepts of identifying, engaging with and enhancing social support for a positive change in substance use. SBNT consists of a series of core and elective topics used within sessions and illustrated in the theory of change model (Figure 3). Core strategies include identifying young people’s social networks, improving communication and coping mechanisms, and given the nature of substance misuse, developing a network-based relapse management plan. The therapeutic approach also has scope to address client-focussed elective areas, for example educational requirements or, when relevant, other important areas such as risk taking.

SBNT has been shown to be effective and cost effective in reducing alcohol usage in harmful adult drinkers.[^36^](#_ENREF_36)^,^ [^60^](#_ENREF_60) On-going work with one of the participating services in the proposed application (Drug and Alcohol Service- Drug and alcohol Newcastle)[^61^](#_ENREF_61) has shown that SBNT is well received by young people aged 12 to 18 who are not in the LAC system.

Figure 4 BDI Theory of change model for SBNT

**
[figure not shown]
**

